### Assessment of Distress

To assess patient stress, questionnaires and vital/laboratory parameters will be used. The day before surgery, after they provide informed consent, the patients will complete initial questionnaires. These include the Spielberger State-Trait Anxiety Inventory (STAI; Hogrefe Verlag), which measures both “trait anxiety” (a general predisposition to anxiety) and “state anxiety” (anxiety related to the current situation, ie, the upcoming surgery) [11]. This questionnaire is often used to measure anxiety and is seen as an indicator of distress. The score is used in many types of analysis, although the trait sections of the STAI are believed to measure negative affectivity rather than trait anxiety per se [12,13]. Additionally, patients will complete the Kurzfragebogen zur aktuellen Beanspruchung (KAB; German for “short questionnaire for acute stress”), which will be repeated perioperatively multiple times to assess changes in response patterns [14]. The focus will be on individual stress trajectories and differences between the control and intervention groups.

For a more objective measurement of stress, the cortisol level in the serum is measured by taking blood samples at multiple times (at baseline, arrival in the operation room, skin incision, clamping the carotid artery, skin suture, and 1 hour after skin suture). Baseline measurements are all taken under consistent conditions: the same time of day before the patient rises from bed. Resting heart rate, KAB score, and the Richmond Agitation-Sedation Scale (RASS) score will be evaluated simultaneously with blood sampling. Cortisol levels are a common tool to measure stress in acute situations [15-17]. The RASS, commonly used in anesthesiology and intensive care, will be used to estimate patients’ agitation and provide insight into their stress levels [18]. Heart rate and RASS scores serve as objective measures of patient stress, while the KAB reflects patients’ subjective burden across 6 categories. This score is frequently used in psychology to capture current stress levels and is well suited for perioperative use due to its ease of administration. The differences in serum cortisol levels between the groups are considered the primary end point. All other measurements are secondary end points.

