#### Clinical Outcomes

In addition to patient satisfaction, anxiety before and during surgery will be assessed. Comparison of patient satisfaction and anxiety measures between the intervention and control groups will be conducted. Additionally, patients in the intervention group will be asked at the end of the operation day whether they would choose to use the goggles again during potential follow-up surgery. For these patients, the average STAI score will be compared between those who would opt to use the goggles again and those who would not. Furthermore, comparisons of the recorded vital parameters and scores at different time points during surgery will be made between the control and intervention groups.

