### Planned Analysis

The analysis will be conducted using SPSS. Due to the study’s exploratory nature, descriptive statistics will be applied. Appropriate measures of central tendency and variability will be used depending on the level of measurement. Graphical representations will be made using line graphs or box plots.

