### Conclusions

This pilot study explores the implementation of video goggles during carotid surgery under conscious sedation and aims to identify suitable outcome parameters for evaluating this interventin’s potential benefits in reducing perioperative stress.

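### RASS is read as a stress measure although the scale runs from agitation to sedation, so a mean or median can mask a difference in agitation or make a more sedated arm look less stressed

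*Protocol article*

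**What the plan says.** Under Assessment of Distress, the protocol article states that "The RASS, commonly used in anesthesiology and intensive care, will be used to estimate patients’ agitation and provide insight into their stress levels". It goes further a little later: "Heart rate and RASS scores serve as objective measures of patient stress". The scale's full name appears in the sentence on timing: "Richmond Agitation-Sedation Scale (RASS) score will be evaluated simultaneously with blood sampling". Cortisol is the primary end point, and "All other measurements are secondary end points", so RASS is secondary.

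Under Clinical Outcomes, "comparisons of the recorded vital parameters and scores at different time points during surgery will be made between the control and intervention groups". Planned Analysis gives a single rule for all measures: "Appropriate measures of central tendency and variability will be used depending on the level of measurement", and "Graphical representations will be made using line graphs or box plots". No statistic is named for RASS.

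The Discussion's Conclusions describe "carotid surgery under conscious sedation". The section on strengths and limitations says that drug administration was recorded because drugs could confound the measurements. It does not say how that record will be used when RASS is read.

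**The concern.** A stress measure should rise with stress and fall without it. A scale that passes from agitation through a neutral point to sedation does that on one side only. Moving from agitated to neutral is less agitation. Moving from neutral to sedated may only mean that a drug was given. The article assigns the whole score to stress and leaves the sedated side without a meaning.

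Two misreadings are then possible. Two arms that differ in agitation can share the same mean or median. Or an arm with more sedated patients can have the lower score and be taken as less stressed. The second has a plausible direction here: the Discussion's Summary remarks that distraction in general may lower the use of sedatives. If that happened in this trial, control patients could score lower because of drugs, and the comparison would tilt against the goggles.

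The stake is the second objective, finding which parameters can capture a benefit. The Sample Size Estimation section makes the results a basis for a confirmatory trial, so a misread RASS would feed into that choice.

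**Working it through.** The article gives no RASS figure to reproduce, and the total of 100 patients has no formal calculation behind it. The check is therefore an illustration.

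**Inputs.** From the article: 100 patients allocated 1:1, so 50 per arm (Randomization), and the two poles, from the scale's name. Assumed: all the distributions below, and a coding of +1 agitated, 0 neutral, -1 sedated. The article does not give the scale's range or anchors.

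**Step 1, the mean.** Let A and S be the agitated and sedated shares in an arm. Then

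mean = A - S, and control minus goggles = (difference in A) - (difference in S).

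The difference in means equals the difference in agitation only if the sedated shares are the same in both arms. Any difference in sedation is subtracted from it.

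**Step 2, the median.** It is 0 whenever fewer than half of the arm are agitated and fewer than half are sedated.

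**Step 3, the SD.** SD = sqrt[(50(A + S) - 50 × mean²) / 49]. It depends on A + S and on the squared mean, so exchanging A and S leaves it unchanged.

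**Step 4, numbers.** Counts are agitated/neutral/sedated out of 50.

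| Assumed arm | Counts | Mean | SD | Median | Quartiles |
|---|---|---|---|---|---|
| Goggles | 2/46/2 | 0.00 | 0.29 | 0 | 0 to 0 |
| Control (a) | 10/30/10 | 0.00 | 0.64 | 0 | 0 to 0 |
| Control (b) | 15/20/15 | 0.00 | 0.78 | 0 | -1 to +1 |
| Control (c) | 15/30/5 | +0.20 | 0.61 | 0 | 0 to +1 |
| Control (d) | 20/30/0 | +0.40 | 0.49 | 0 | 0 to +1 |
| Control (e) | 5/30/15 | -0.20 | 0.61 | 0 | -1 to 0 |

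**Step 5, reading the table against the goggles arm.**

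- (a): agitation differs by 20% - 4% = 16 points and sedation by the same 16 points, so the means differ by 0. Median and quartiles also agree. Only the SD separates the arms, 0.64 against 0.29.
- (b): the means again agree, but both the SD and the quartiles show a difference.
- (c): agitation differs by 26 points and sedation by 6, so the means differ by 0.26 - 0.06 = 0.20. The difference is diluted, not lost.
- (d): with no sedation in control, nothing is masked: 0.36 + 0.04 = 0.40.
- (e): agitation is 6 points higher in control (10% against 4%), yet the mean is 0.06 - 0.26 = -0.20. Read as stress, control looks better although more of its patients are agitated.
- (c) and (e) have the same SD, 0.61, although one leans to agitation and the other to sedation.
- The median is 0 in every row, so choosing it for an ordinal score does not help.

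**Step 6, precision of the proposed share.** Wilson 95% limits are [p + z²/2n ± z × sqrt(p(1-p)/n + z²/4n²)] / (1 + z²/n), with z = 1.96 and n = 50. For 2/50: (0.0784 ± 0.0665)/1.0768, about 1% to 13%. For 10/50: (0.2384 ± 0.1173)/1.0768, about 11% to 33%. The share is interpretable but imprecise.

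**The case against.** The strongest reply is that the plan does not fix a mean for RASS at all. The generic rule defers to the level of measurement, an ordinal score need not be averaged, and detail on a secondary end point may sit in an analysis plan that is not shown. That stands against any claim that the article prescribes an averaged RASS. It does not answer the point that the article itself reads the whole score as stress, and the median does not repair that reading.

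A reader might infer that agitated and sedated patients cancel out and that a real difference disappears. The documents do not support this. Variability and box plots are planned alongside central tendency. The spread differs even in scenario (a), and the quartiles give the direction in (c) and (e). Full cancellation needs the differences in agitation and sedation to be equal; otherwise the effect is diluted or shifted, and if sedation is the same in both arms nothing is masked.

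Sedation in this trial is also only lightly documented. The Methods describe a cervical block and say that the study does not alter anesthetic management; one phrase in the Conclusions refers to sedation, without a frequency. Drug use was recorded, so confounding was partly foreseen. Staff also rate calmness on a separate scale, but once and after surgery, so that rating does not correct RASS at each time point. Finally, the article contains no rule by which a parameter is kept or dropped on its RASS mean, so a wrong choice for the later trial is a risk and not a forecast.

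**Conclusion.** The concern holds in a limited form. The article treats a scale with two opposite poles as a stress measure, gives the sedated side no meaning, and offers only a generic summary that does not separate the poles. A mean or median can then mask a difference in agitation, as in scenarios (a) and (b), or reverse it, as in (e).

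This rests on two assumptions that the article does not settle: that some patients score on the sedated side, and that the sedated share differs between arms. The distributions are illustrative, so no size can be put on the effect in the actual data. A claim that the planned analysis must miss a real difference would go too far, because the spread is reported too. RASS is a descriptive secondary end point in a pilot, so the priority is modest; what raises it above a detail is the stated aim of identifying parameters for later research.

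**What to change.** For each arm and each time point, report the shares of patients on the agitated side, at the neutral point and on the sedated side, using the scale's own anchors. State that only the agitated share is read as the stress indicator. Show the sedated share next to the documented drug use, so that a low score can be recognised as a possible drug effect. A mean or median RASS, if shown, should not be interpreted as stress on its own. In Assessment of Distress, narrow the description of RASS as an objective stress measure to its agitated side.

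The cost is a change of wording and one table. RASS is already recorded at each time point, and the analysis follows inclusion of the 100th patient, so no new data are needed. The downside is that agitation may be rare in awake, cooperative patients and its share imprecise, as the intervals above show; it should be reported with its interval.

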### Assessment of Usefulness and Practicality

Postoperatively, the patients and the surgical team (the first surgeon and attending anesthesiologist) will complete a satisfaction survey using a 10-point numerical rating scale (NRS). Surgeons and anesthesiologists will rate the patients’ manageability, relaxation, and calmness during surgery. Patients will also rate the satisfaction and anxiety they experienced before and during surgery on a 10-point NRS scale. Patients in the video goggle group will be asked if they would choose to use the goggles again in a potential follow-up operation (as a dichotomic yes/no question). Motion sickness when using the goggles, a significant issue associated with immersion in virtual reality, will be assessed.

### Outcomes

#### Primary Feasibility Outcomes

Patients who meet the inclusion criteria and agree to participate are enrolled in the study. Patients who meet the criteria but decline participation are counted anonymously, with differentiation between those who refuse and those who are excluded for other reasons (eg, language barriers, profound hearing impairment, dementia, or logistical challenges). After the operation is completed and the patient leaves the wake-up room, all data are checked for completeness, and an attempt is made to fill in any missing data. If there any adverse events or remaining missing data, or if the patient withdraws consent to participate in the study, the collected data are excluded from analysis. Because of the very short time from patient inclusion to complete data collection for each patient and because there is no follow-up after the initial inpatient stay, we assume that this method will yield mostly complete records.

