### Randomization

Patient randomization follows a predefined list based on patient ID, assigning them to either the control or intervention group. The list is followed sequentially, and random assignment to either the intervention or control group is performed using Microsoft Excel. The randomization scheme is constructed to ensure a 1:1 allocation ratio (50-50) upon reaching a total sample size of 100 patients. Due to the nature of the intervention, blinding of participants and investigators is not feasible.

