### Data Collection and Management

Missing data are not expected; however, if data are incomplete for a participant, the participant will be excluded from the analysis. Group allocation and reasons for exclusion will be reported transparently to minimize the risk of bias. Due to the pilot nature of the study, no imputation is planned.

Patient-specific data and collected parameters are recorded on paper case report forms and later manually entered into a Microsoft Excel database. The complete dataset will be transferred to an SPSS (version 28, IBM Corporation) database for analysis. Digital data are stored in a folder with restricted access on a protected server of the University Hospital Augsburg. Paper-based data are stored in a locked office at the study office. Final data access is only granted to primary investigators.

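### The rule for filling in missing values after the wake-up room does not exempt the KAB and RASS ratings, which are valid only if recorded at their own time point

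*Protocol article*

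**What the plan says.** All references are to the Methods of the protocol article.

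- **Completion rule (Primary Feasibility Outcomes).** The check comes late, when surgery is over and the patient has left the wake-up room: "all data are checked for completeness, and an attempt is made to fill in any missing data". The sentence covers all variables. It names no permitted source and no marking of late entries.
- **Timing rule (Assessment of Distress).** "Resting heart rate, KAB score, and the Richmond Agitation-Sedation Scale (RASS) score will be evaluated simultaneously with blood sampling". The sampling times are "at baseline, arrival in the operation room, skin incision, clamping the carotid artery, skin suture, and 1 hour after skin suture".
- **Nature of the ratings (same section).** KAB is self-reported: "the KAB reflects patients’ subjective burden across 6 categories". RASS is classed with heart rate as an objective measure. Serum cortisol is the primary endpoint and everything else is secondary.
- **Cost of a remaining gap (Data Collection and Management; also Primary Feasibility Outcomes).** "if data are incomplete for a participant, the participant will be excluded from the analysis". No imputation is planned.
- **Blinding (Randomization).** "blinding of participants and investigators is not feasible".
- **Use of the values (Clinical Outcomes, Planned Analysis).** Scores are compared between arms by time point, with descriptive statistics.

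**The concern.** KAB and RASS describe a state at one moment, such as skin incision or clamping. When completeness is checked, those moments are over. A missing heart rate may still be on the anesthesia record, and a missing cortisol result may be in the laboratory system. A KAB that was not asked, or a RASS that was not scored, exists nowhere and could only be recollected.

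The patient knows the arm and how the operation went, and so do the staff. Under Interventions, it is the anesthesiologists who mainly help patients with the goggles. A recollected rating may be coloured by both. Without a marker it would enter the KAB or RASS course as if it had been taken on time. The exclusion rule gives a reason to fill the gap, because one empty cell otherwise costs the whole record, including its cortisol series.

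At stake is the by-time-point comparison of KAB and RASS between arms. A later confirmatory trial is meant to build on these results.

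**Working it through.** There is no figure in the plan to reproduce: the 100 patients were set without a formal calculation and the analysis is descriptive. The main check is a comparison of the rules. Two illustrations on assumed inputs follow.

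**Step 1. The rules side by side**

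| Measure | Required timing | Possible source after the wake-up room |
|---|---|---|
| Cortisol | six blood samples | laboratory result, if the sample was drawn; cannot be recalled |
| Heart rate | with each sample | monitor or anesthesia record |
| RASS | with each sample | a score already charted at that time; otherwise recall |
| KAB | with each sample | a form completed at that time; otherwise recall |
| Satisfaction and anxiety NRS, staff ratings, goggles-again question | postoperative by design | can legitimately be completed then |

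Read literally, the completion rule covers every row. For an unrecorded intraoperative KAB or RASS, it allows an entry that the timing rule does not.

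**Step 2. How strong is the pressure to fill?**

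Assume that each value is missing independently with probability p. The share of patients with at least one gap among k values is 1 − (1 − p)^k. The article gives no p and says that missing data are not expected.

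- KAB and RASS: k = 6 × 2 = 12.
- KAB, RASS, heart rate and cortisol: k = 6 × 4 = 24.

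| p | k = 12 | k = 24 |
|---|---|---|
| 0.5% | 5.8% | 11.3% |
| 1% | 11.4% | 21.4% |
| 2% | 21.5% | 38.4% |
| 5% | 46.0% | 70.8% |

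These are patients who would have to be completed or dropped. The table shows why there is an incentive to fill. It does not measure recall bias, because a dropped patient contributes none and a gap closed from a chart contributes none.

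**Step 3. How large could the bias be at one time point?**

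Let f be the share of KAB values supplied by recall. Let d be the shift that recall adds to the arm difference among those values, in SD units. Then bias = f × d. With 50 patients per arm, the standard error of the difference is √(2/50) = 0.20 SD.

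- f = 5%, d = 0.3: bias 0.015 SD, and 0.015/0.20 = 0.075 standard errors.
- f = 10%, d = 0.5: bias 0.05 SD, or 0.25 standard errors.
- f = 20%, d = 1.0: bias 0.20 SD, or 1.0 standard error.

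Both f and d are assumptions. The result is negligible at the low end and material at the high end. Without a marker on late entries, a reader could not tell which end applies.

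**The case against.** The strongest reply is that nothing in the article mentions memory. A check of paper forms against the anesthesia record and the laboratory system is an ordinary step, and at least as natural a reading. The article goes on to provide for data that remain missing, so it does not demand that every gap be closed. Several items are collected after surgery anyway and can properly be completed then. Permitted sources and the dating of late entries may be set out in the full protocol. Knowledge of the arm also colours ratings made on time, so only the additional effect of recall belongs to this rule.

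Most of this stands. A reader might infer that the protocol has ratings reconstructed from memory, and the text does not support that. A reader might also take the shares in Step 2 as a count of recalled records, which they are not. The exposure is confined to secondary endpoints, and it is not shown that the aim of identifying suitable parameters is undermined.

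What the reply does not remove is the wording of the rule. The article does more than stay silent on sources: it states a rule for all missing data, applied after the intraoperative moments have passed, next to a requirement that two of the measures be taken at those moments. Chart retrieval cannot help where no rating was made.

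**Conclusion.** The point holds in a limited form. As written, the completion rule permits late KAB and RASS entries that conflict with the timing rule. Unblinded raters and whole-patient exclusion make such entries both prone to bias and tempting. Whether any have been or will be made cannot be known from the article.

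The possible bias concerns secondary endpoints in a descriptive pilot. Its size cannot be derived from the document. The range of 0.015 to 0.20 SD (0.075 to 1.0 standard errors) rests wholly on the assumed shares and shifts, and the bias is small if late entry is rare. The cortisol values are not affected, since they cannot be recalled. The postoperative NRS ratings are retrospective by design and are not part of the problem. The change is nevertheless worth making before analysis, because it is cheap and removes the doubt.

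**What to change.** In the protocol or analysis plan:

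1. Allow late completion only from a contemporaneous source (anesthesia record, laboratory system, or a rating already charted at that time) and for items that are postoperative by design.
2. Leave intraoperative KAB and RASS values missing if they were not recorded at their time point.
3. Keep the patient and analyse each endpoint with all available time points, instead of excluding the whole record. This also removes the incentive to fill.
4. Where the paper forms show a late entry, flag it, report the number by arm, and repeat the KAB and RASS summaries without those values.

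**Cost.** A short addition to the text, a database flag and one repeated set of summaries. A few more KAB and RASS cells will be empty. Recruitment was about 90% complete at submission, so roughly 90 of the 100 patients were already enrolled (0.90 × 100). For them, late entries may not be identifiable from the forms, and the report should say so. Analysis begins only after the 100th patient, so the rule can still be settled beforehand.

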**Methods:**

This prospective, randomized study at the University Hospital Augsburg is evaluating the use of HappyMed video goggles by patients undergoing carotid endarterectomy under regional anesthesia. Participants are randomized into either the intervention group, which receives the video goggles, or the control group, which does not. The surgical and anesthetic procedures remain consistent across both groups. Patients are eligible if they meet the surgical criteria, are able to lie supine, and are cooperative. Patients are excluded if they are receiving corticosteroids, have dementia, or have a language barrier. The study uses questionnaires and vital/laboratory parameters, including cortisol levels and heart rate, to assess stress and anxiety. To monitor potential motion sickness, the occurrence of nausea or vomiting is documented. Both patients and surgical staff will evaluate the experience postoperatively to determine the goggles’ impact on patient experience and stress management during surgery.

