## Methods

### Trial Design and Study Population

In this prospective, randomized study, the use of the HappyMed video goggles (HappyMed GmbH) will be evaluated in patients undergoing carotid endarterectomy under regional anesthesia. The study is being conducted as a single-center study at the University Hospital Augsburg (Augsburg, Germany) in collaboration with the departments of vascular surgery and anesthesiology. Patient acquisition started in September 2022 and should be completed within three years. All patients scheduled for the abovementioned procedure who meet the inclusion criteria are informed about the study and invited to participate. Upon agreeing to participate, patients are randomized according to a predefined list, assigning them to either the intervention group (with video goggles) or control group (without video goggles). The surgical procedure is identical for both groups, and the study does not influence the operative or anesthetic management of the patients.

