### Secondary Exclusion Criteria and Adverse Events

Patients who withdraw consent after enrollment will be excluded from the study. If complications arise during surgery requiring conversion to general anesthesia, patients will also be excluded.

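### Patients are dropped after randomisation for adverse events, conversion to general anesthesia or incomplete data, which can bias the arm comparison and conflicts with assessing motion sickness

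*Protocol article*

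**What the plan says.** Allocation comes before surgery (Trial Design and Study Population): "Upon agreeing to participate, patients are randomized according to a predefined list". The target is 50 per arm (Randomization): "The randomization scheme is constructed to ensure a 1:1 allocation ratio (50-50) upon reaching a total sample size of 100 patients". The same section says that participants and investigators cannot be blinded.

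Three passages then remove randomised patients:

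- Primary Feasibility Outcomes: a patient's data are left out under the condition "If there any adverse events or remaining missing data, or if the patient withdraws consent". The type, severity and relatedness of the event are not restricted.
- Secondary Exclusion Criteria and Adverse Events: "If complications arise during surgery requiring conversion to general anesthesia, patients will also be excluded". Patients who withdraw consent are also excluded.
- Data Collection and Management: a participant with incomplete data is left out and nothing is imputed. Allocation and the reasons for exclusion are to be reported.

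The primary end point is the between-group difference in serum cortisol (Assessment of Distress). Motion sickness is also an outcome (Assessment of Usefulness and Practicality): "Motion sickness when using the goggles, a significant issue associated with immersion in virtual reality, will be assessed". According to the Methods part of the Abstract, it is captured because "the occurrence of nausea or vomiting is documented". Strengths, Limitations, and Dissemination gives the main aims as feasibility, acceptance by patients and staff, and finding good parameters for later research.

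**The concern.** All these exclusions except the baseline part of the missing-data rule depend on what happens after allocation. Goggles could plausibly cause nausea, be poorly tolerated, or raise or lower distress. Distress in turn could be linked to complications or to incomplete measurements. If exclusion differs between arms and is related to stress, the patients compared are no longer the randomised groups, and a cortisol difference can appear or disappear without any effect of the goggles. The completeness check is made after surgery by people who know the allocation, and the term for adverse events is not defined, so there is room for judgement about who is removed.

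Two further things are at stake. Whether patients would use the goggles again would be summarised mainly in those for whom nothing went wrong. And nausea or vomiting, the recorded sign of motion sickness, is an adverse event in ordinary usage, so the rule can remove the very patients that this outcome is meant to count. Sample Size Estimation says the results are to be the basis for a confirmatory trial, so a distorted estimate would be carried forward.

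**Working it through.** The plan gives no event rates, SD or effect size, so it has no figure to reproduce. The inputs from the document are 50 patients per arm, allocation before surgery and no blinding. All exclusion rates and links to stress below are assumptions. Cortisol is in SD units, the true effect is zero, and differences are goggles minus control, so a negative value is a spurious benefit.

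**Model A: fixed shift.** A proportion p of an arm is removed, and those removed average δ SD above the arm mean. Since pδ + (1 − p)m = 0, the mean of those kept is m = −δp/(1 − p). With the same δ in both arms, the bias is −δ[p₁/(1 − p₁) − p₀/(1 − p₀)], where 1 is goggles and 0 is control.

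**Model B: latent cut-off.** A patient is removed when a latent variable with correlation ρ to cortisol exceeds a cut-off c, with exclusion rate e. The mean of those kept is −ρφ(c)/(1 − e). The factor φ(c)/(1 − e) is 0.109 at 5%, 0.274 at 15% and 0.424 at 25%.

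| Model | Control excluded | Goggles excluded | Assumed link | Bias (SD) |
|---|---|---|---|---|
| A | 5% | 10% | δ = 1 | −(0.111 − 0.053) = −0.058 |
| A | 5% | 20% | δ = 1 | −(0.250 − 0.053) = −0.197 |
| B | 5% | 15% | ρ = 0.3; 0.5 | −0.050; −0.083 |
| B | 5% | 25% | ρ = 0.3; 0.5 | −0.095; −0.158 |
| B | 15% | 5% | ρ = 0.3; 0.5 | +0.050; +0.083 |
| B | equal rates (5% or 10%) | same | any ρ | 0 |
| B | any | any | ρ = 0 | 0 |

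These are illustrations, not bounds. Model B at 10% against 5% with ρ = 0.3 gives only 0.3 × (0.195 − 0.109) ≈ 0.026 in size. Model A at 25% against 5% with δ = 1 gives 0.333 − 0.053 = 0.28. Equal rates alone do not protect: with 10% removed in each arm, δ = 1 in controls and δ = 0 with goggles, the bias is 0.10/0.90 = +0.11.

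For scale, a 95% interval for the difference with 50 per arm has half-width 1.96 × √(2/50) = 0.39 SD.

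**Acceptance.** Suppose 36 of 50 goggle patients would use them again (72%) and 10 are removed. If all 10 would decline, the analysed figure is 36/40 = 90%. This is the worst case. If those removed answer like the rest, it stays at 72%.

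**Motion sickness, literal reading.** Every affected patient is removed, so the analysed count is 0 whatever the true rate. At assumed true rates of 5%, 10%, 20% and 30%, the expected cases among 50 are 2.5, 5, 10 and 15. The chance of at least one case, 1 − (1 − rate)^50, is 0.92 at 5% and 0.995 at 10%. At 30%, about 35 patients remain with no events, and the one-sided 95% upper limit would be 1 − 0.05^(1/35) = 8.2%, far below the assumed truth.

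**Incomplete data.** Cortisol, heart rate, KAB and RASS are taken at six times, so 4 × 6 = 24 items. Read literally, one missing item removes the patient. A converted patient cannot give awake ratings afterwards, so the missing-data rule would remove that patient even if the conversion rule were deleted.

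**The case against.** The best defence is that this is a descriptive pilot with no formal sample size and no confirmatory claim, and that Data Collection and Management promises allocation and reasons for exclusion. Leaving conversions out of an awake-surgery stress trajectory is also reasonable as one labelled analysis, because general anesthesia ends the condition under study. This lowers the consequence but does not remove the problem. Descriptive means and proportions are distorted by selection just as tests are, and reporting who was removed does not put them back. Nor is this a detail left to an analysis plan, because the article itself fixes the rule.

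Three stronger readings are tempting, and the documents do not support them.

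- *The comparison is biased, and in favour of the goggles.* No event rates are given. Size and direction are unknown, and more exclusions among controls would work against the goggles. Nothing suggests that goggles cause or prevent neurological events at clamping.
- *Motion sickness becomes unobservable.* Nausea and vomiting are still documented, and a count could be recovered from the reported reasons for exclusion. Adverse events are undefined, and the section with that term in its heading lists only consent withdrawal and conversion. On that narrow reading, patients with nausea stay in. The sentence under Primary Feasibility Outcomes has no such limit, however, so the text needs settling.
- *Feasibility is estimated only in patients without problems.* The counts of enrolled, refusing and ineligible patients are untouched by the rule.

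Larger figures also fail. Removing 20% against 5% with those removed 1.5 SD above average would give 1.5 × 0.197 = 0.30 SD, but under normality even the highest 20% average only φ(0.842)/0.20 = 1.40 SD. The δ = 1 case at 20% already needs a correlation of about 1/1.40 = 0.71, so 0.20 SD belongs at the strong end.

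**Conclusion.** The concern stands in a limited form. The exclusions act after randomisation, in an unblinded trial, with no all-randomised analysis described, so they can bias the cortisol comparison in either direction. Under the assumed rates (5% in one arm, 10% to 25% in the other) and a moderate to strong link with stress, the bias is about 0.05 to 0.20 SD with no true effect. At most that is about half of the 0.39 SD sampling half-width, but more patients would not reduce it. It is zero when exclusion is equal and by the same mechanism in both arms, or unrelated to stress. Acceptance can be overstated by an amount that depends on how those removed would have answered. The conflict with the motion-sickness aim rests on the literal reading of adverse events, and the passages should be reconciled whichever reading was meant.

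**What to change.** Change Primary Feasibility Outcomes, Secondary Exclusion Criteria and Adverse Events, and Data Collection and Management together. Changing only the first two would leave the incomplete-data rule to remove the same patients.

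- Analyse all randomised patients in their assigned arm with all available data. For conversions, use stress measures up to conversion. Do not delete a whole patient for a missing item.
- Report adverse events, nausea or vomiting, and conversion by arm with all randomised patients as denominator. Report early goggle removal in the goggle arm.
- Leave out only patients who withdraw permission to use their data, and count them by arm.
- Keep the present exclusion rule as a labelled sensitivity analysis, with adverse events defined.

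The cost is a late change to the analysis text of an ethics-approved study with about 90% of recruitment done, which should be dated and made before the data are analysed. Data already collected for patients set aside must also be entered, where the forms were kept. The documents do not say whether they were.
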